## Abstract

**Background:** Major depressive Disorder (MDD) is a severe mental disorder associated with considerable disability and high costs. Over the last decades, various psychotherapies for MDD have been developed and researched, among others Behavioral Activation (BA) and Metacognitive Therapy (MCT). MCT and BA target different maintaining factors of MDD and have not been compared to date. The PRO^*^MDD randomized controlled trial will compare MCT and BA in the routine clinical setting of an outpatient clinic.

**Methods and Design:** We aim to recruit 128 MDD patients, who will be randomly assigned to either MCT or BA. In both conditions, patients will receive one individual therapy session and one group therapy session per week for a maximum of 6 months. Assessments will take place at baseline, pre-treatment, mid-treatment, post-treatment as well as at 12, 18, and 30 months after start of treatment as follow-up. The primary outcome is reduction of depression severity assessed with the Hamilton Rating Scale for Depression; secondary outcomes address quality of life, psychosocial functioning and participation as well as comorbidity.

**Discussion:** The PRO^*^MDD study is the first randomized controlled trial to compare the effectiveness of MCT and BA. The outcome of this trial will increase our knowledge on the effectiveness and applicability of both treatment modalities and therefore contribute to the improvement of treatment for depressive patients.

**Ethics and dissemination:** The study has been reviewed and approved on 11 August 2016 by the Ethics Committee of the Lübeck University (reference number: 16–176). The results will be discussed through peer-reviewed publications.

**Trial registration:** German Clinical Trials Register DRKS-ID: DRKS00011536 (retrospectively registered)

## Introduction

Depressive disorders range among the most common and disabling psychiatric disorders worldwide. The Global Burden of Disease Study (WHO) identified depression as one of the main causes for disability, accounting for a major part of the global burden of disease (1, 2). The lifetime prevalence of depression has been estimated at 12% in Germany (3) and 17% in the US (4) and the life expectancy of depressed patients is markedly shortened, with women expected to live 12 years and men 16 years shorter than men and women without depressive disorders (5). Approximately 60% of patients that experienced one depressive episode will develop a recurrent depressive episode and every recurring episode increases the risk of further depressive episodes (6–9). About one third of depressive patients develop chronic depression (DSM-5 “persistent depressive disorder”), with depressive symptoms persisting for 2 years or longer (10, 11). Depressive disorders are often accompanied by suicidality as well as psychiatric and somatic comorbidity (12–15). This indicates a great need for adequate treatment of this patient population.

Over the last decades, psychotherapeutic and psychopharmacological treatment options for patients with depression have improved and new treatment methods have been developed and implemented. However, research has indicated that only one in two patients with depression in Germany receives adequate treatment^1^ (16) and one quarter of patients with severe depressive disorders lack specialist outpatient treatment (17). Treatment of depression, especially inpatient treatment, is associated with high direct medical costs and recurrent depressive episodes are associated with a cost increase of 50% (18). Also, depression reduces the level of functioning and participation in working life, therefore accounting for a substantial loss of productivity (17) and indirect costs (18–20). Thus, the development of outpatient treatment programs for depression is much needed. This research study aims to investigate the effect of outpatient treatment programs on depressive symptoms, psychosocial functioning and quality of life by comparing two innovative and promising Behavioral Activation (BA) (21) and Metacognitive Therapy (MCT) (22) .

According to national guidelines (23), patients with depressive disorders are treated with psychopharmacological (antidepressant medication) or psychotherapeutic methods or a combination of both, depending on the severity of the depressive disorder. The importance and efficacy of psychotherapeutic methods in the treatment of depression has been well-investigated and established in over 200 randomized controlled trials (RCTs) (24–27). The method that has been investigated most is cognitive behavior therapy (CBT) which has proved effective compared to a number of control conditions such as waitlist, psychopharmacotherapy, placebo, supportive contacts, and other psychotherapeutic treatment methods. However, remission- and response rates of existing psychotherapeutic treatments for depression indicate that only half of the patients treated by CBT reach remission of their depressive disorder, and that relapse is frequent (28–30). This calls for improvement and optimization of existing treatments for depression.

A promising strategy for optimizing therapy outcome is the development based on research of treatment components which address central psychological mechanisms maintaining depression. Thus, in this study we compare BA and MCT, two methods which target different processes underlying depression, have few overlapping therapy techniques and teach patients a different set of skills (see methods for more details).

Behavioral Activation (BA) is a well-established evidence-based cognitive behavioral method, which has been revised in the course of the “third wave” of CBT (31). BA addresses the loss of positive reinforcements due to avoidance behavior in depression and uses techniques to help patients increase the rate of value-based behavior to foster access to long-term positive reinforcements. In several meta-analyses, the latest including 26 RCTs, BA proved superior to control conditions (waitlist, treatment as usual, psychopharmacotherapy) and comparable to CBT regarding the reduction of depressive symptoms (32–35). The revised manual of BA, which was developed in the course of the “third wave” of CBT, was investigated by a large-scale RCT including 241 patients which compared BA to antidepressant medication and CBT. All treatment methods proved comparable for patients with mild depressive episodes. For patients with moderate and severe depressive episodes, BA and antidepressant medication proved superior to CBT. However, in the BA condition, attrition rate was lower than in the antidepressant condition (36). At 2 year follow-up, patients that responded to therapy showed comparable relapse rates in all conditions. Discontinuation of medication was associated with a poorer prognosis (37).

Metacognitive Therapy (MCT), developed by [name] at the University of Manchester, UK is a therapy method based on an empirically tested model of psychological disorders. MCT focusses on dysfunctional metacognitive processes central to the development and maintenance of depression (22). Treatment techniques aim to change dysfunctional metacognitions (thoughts/beliefs about cognitive processes) and to reduce related dysfunctional cognitive processes (rumination, worrying, threat-monitoring, and dysfunctional coping strategies) that are summarized as a “Cognitive-Attentional-Syndrome” (CAS). Several research studies showed high effectiveness of MCT in individual as well as in group settings. In small case studies, MCT was associated with a reduction of depressive symptoms after a small number of sessions (38–41). In a small RCT, MCT proved superior to treatment as usual in the reduction of depressive symptoms (42). An Australian RCT conducted independently of the MCT developers compared MCT to CBT. Both conditions showed a reduction of depressive symptoms with moderate to high effect sizes but failed to show a difference between CBT and MCT, which may be due to the small sample size (*N* = 48) (43). A small Iranian RCT including 33 patients with depression compared MCT to CBT and antidepressant medication. MCT and CBT proved more effective than psychopharmacotherapy in the reduction of depressive symptoms, rumination and anxiety (44). MCT seems to be as effective as CBT while requiring fewer therapy sessions. One recent meta-analysis concluded that MCT might be superior to CBT in the treatment of anxiety and depression (45), but more studies are needed.

To date, there are few RCTs on MCT for depression (42–44), and “real-world” studies in regular outpatient therapy settings on both MCT and BA are scarce. Also, there have been no comparative studies on MCT and BA.

The major objective of this study is to compare the effectiveness of MCT and BA in the treatment of patients with moderate or major depressive disorders in a routine German outpatient setting. As this is the first study that compares MCT and BA, it serves as a pilot trial intended to generate preliminary data for orientation and hypothesis generation. The primary hypothesis is that MCT and BA differ significantly in reducing depressive symptoms (two-sided hypothesis). A two-sided hypothesis was chosen because MCT and BA have never been compared to date and the existing literature does not allow predictions on the directionality of any difference between the two methods. Secondary outcomes address general psychopathology, psychiatric comorbidity, quality of life, psychosocial functioning, and attrition. In addition, we undertake a secondary process evaluation to investigate the moderating and mediating factors in BA and MCT that influence outcome. We will also be conducting a time to event analysis as MCT is often said to be particularly quick in inducing remission.

## Methods and design

### Design

The study is designed as a randomized controlled trial (RCT). Patients will be assigned to one of the two active treatment conditions (MCT or BA).

We aim to investigate the “real world” effectiveness of the two treatments, therefore the PRO^*^MDD study is conducted in the routine clinical setting of an outpatient clinic. As such, we use minimal exclusion criteria, set low barriers for patient participation and guarantee the clinical equipoise of the two treatment programs. Thus, we minimize resistance for participating in a clinical trial with randomization. The PRO^*^MDD trial adheres to the SPIRIT guidelines and methodology (46). For an overview on study design see the flow chart of enrolment, intervention and assessment in Figure 1.

**Figure 1 F1:**
[figure not shown]
Flow chart of study design. MCT, Metacognitive Therapy; BA, Behavioral Activation.

### Setting

Participants will be recruited within the outpatient center of the Department of Psychiatry and Psychotherapy of the Lübeck University Hospital in Germany. The outpatient clinic of the Department of Psychiatry and Psychotherapy treats approximately 510 patients with depressive disorders per year. The department is specialized in treating severely ill patients, often with multiple comorbidities; therefore we included patients with moderate to severe depressive episodes and decided for a maximum treatment duration of 6 months. Potential participants that meet the inclusion criteria are informed about the PRO^*^MDD study during the regular intake procedure verbally and with written information. If they agree to participate and give informed consent, they will be invited for a screening to assess in- and exclusion criteria.

### Eligibility criteria

Patients aged 18 or above will be included if they (1) have a main diagnosis of a depressive episode [as diagnosed by the Structural Clinical Interview for DSM-IV (SCID I)] (2) have a depression severity score of 16 or higher measured by the 24-item Hamilton Rating Scale for Depression (HRSD-24) (3) have read and signed an informed consent form, (4) are able and willing to participate reliably in therapy and assessment procedures. Exclusion criteria are (1) lifetime diagnosis of a psychotic or bipolar disorder, (2) intellectual deficits (IQ < 85), (3) acute suicidality, (4) a main diagnosis other than MDD that requires prioritized treatment and (5) acute substance dependency (according to DSM-5) that requires detoxification treatment. Participation is possible after completion of detoxification treatment and a 2 month period of abstinence.

### Sample size

The primary outcome measure to test the main hypothesis is the severity of depressive symptoms at post-treatment, assessed by the Hamilton Rating Scale for Depression [HRSD, 24-items version (47)]. Confirmatory two-tailed testing of two conditions requires a sample size of *n* = 64 patients in each condition (total *N* = 128 patients). The sample size calculation (48) is based on a power of 80% and a type I error of 5%, as well as an effect size of *d* = 0.5. The estimated between subjects effect size is set according to the one defined by the National Institute of Clinical Excellence (49) for clinical significant difference (*d* ~ 0.5).

### Randomization

After completion of the baseline assessment, participants are randomised equally (1:1) to the two groups (MCT or BA). Randomisation is stratified by gender to avoid biases due to unbalanced gender distribution. Randomization will be conducted by using the program BiaS (11.02) (50). The allocation is concealed from participants and researchers. After randomization, participants are informed about the start date of the treatment. In the first treatment session participants will be informed about which condition and therapist they are assigned to.

### Intervention

Participants will be randomized to either MCT or BA treatment. The structural conditions in both treatment programs are as similar as possible to guarantee clinical equipoise. In both conditions, treatment duration will be a maximum of 6 months with one individual therapy session (50 min) and one group therapy session (90 min) per week. Patients remitted at the mid-treatment assessment (after 3 months of treatment) can end therapy early. After the 12 months follow up assessment, participants see their study therapist for an evaluation session in which the results of the assessment are discussed and in which further treatment will be planned if necessary. Patients will receive 1–2 individual sessions before the start of group treatment to become accustomed to the treatment model and their therapist and to be prepared for the group sessions. The estimated amount of sessions in the program will be 20–24 individual sessions and 24 group sessions. To date, there is little research on the difference between the effectiveness of combined group and individual therapy vs. individual or group therapy only. For several reasons, we decided to offer a combined group and individual therapy program based on our clinical experience: Adding a weekly group therapy session to weekly individual sessions has the advantage of being able to offer psychoeducation and training of specific skills in a group setting, which leaves enough room in the individual sessions to address personal issues and special needs of the patients. Also, as inclusion takes place every 3 months and treatment duration is 6 months, patients that are new to the group can learn from the patients that have already completed 3 months of treatment. As patients treated in the University Hospital display high chronicity, comorbidity and complex symptomatology, we considered group therapy only to be insufficient.

#### Behavioral activation (BA)

Behavioral Activation (BA) is based on Lewinson's reinforcement model of depression (1974), the first behavioral model for the explanation and treatment of depression. Central to this model is the assumption that a low rate of behavior oriented positive reinforcement triggers and maintains depressive symptoms. This is especially maintained by negatively reinforced avoidance behavior (social withdrawal, low activity rate) and a lack of interpersonal skills. Therefore, the main goal of BA is the structured installation of activities and the reduction of behavior that promotes depression. In the course of the “third wave” of cognitive behavior therapy, the original model has been extended. Instead of just scheduling any activities to increase the patient's activity level, BA is now focusing on the development of skills necessary for engaging in personally meaningful, value-based behavior that allows a long-lasting access to positive reinforcers and leads to a fulfilling life. This requires acceptance of aversive experiences and overcoming avoidance strategies that maintain depressive symptoms. The behavioral change is expected to lead to a positive change in thinking and emotions. Important techniques of BA are self-monitoring strategies like weekly activity schedules that help to relate activities to emotional states and help to plan value-based behavior. In the beginning of BA therapy, learning about individual goals and values is essential to identify value-based behavior. Weekly schedules, planning of activities and contingency management are implemented subsequently to facilitate the installation of value-based behavior. Other techniques are training of interpersonal skills and problem-solving skills.

#### Metacognitive therapy (MCT)

Metacognitive Therapy (MCT) was developed by [name] (22) and assumes that dysfunctional over-thinking processes and biased cognitive control are the underlying factors for the development and maintenance of depressive disorders. Central to the concept of MCT are metacognitions (thoughts/beliefs about cognitive processes) and dysfunctional cognitive processes such as rumination, worry and threat-monitoring as well as dysfunctional coping strategies (e.g., avoidance, thought suppression) that are summarized under the term “Cognitive-attentional-Syndrome” (CAS). The CAS is maintained by positive and negative metacognition (e.g., “rumination helps me find a solution to my problems,” “my depressed thinking is a sign I have lost my mind”). Therefore, the aim in MCT is to change positive and negative metacognitions and to reduce the CAS. This is achieved by formulating a case conceptualization and challenging positive and negative metacognitions and the purpose of rumination and other dysfunctional coping strategies. To help the patient regain flexibility of cognitive control, the patient is introduced to the “Attention Training Technique” (ATT). Another important technique of MCT is “Detached Mindfulness” (DM), in which the patient is enabled to experience thoughts and images, as temporary events without the need of further mental and behavioural enagagement (e.g., rumination, suppression, distraction). In this way, DM helps to develop a new attitude toward internal events. DM is illustrated by a range of metaphors and exercises with the goal to teach patients to identify rumination processes and apply DM on thoughts or beliefs that usually trigger rumination or worry processes. The major differences between MCT and BA are summarized in Table 1.

**Table 1 T1:** Major Differences of MCT and BA.

	**MCT**	**BA**
Case formulation and theory	“Top-down” assumption of development and maintenance of depression and treatment: dysfunctional cognitive processes lead to dysfunctional coping strategies such as rumination, worrying, threat monitoring. In treatment, the installation of functional metacognitive processing is expected to promote functional behavior.	“Bottom-up” assumption of development and maintenance of depression and treatment: low activity rate leads to low positive reinforcement which promotes depressed mood. In treatment, the installation of value-based behavior is expected to help patients get access to stable positive reinforcement and by this promote positive change of emotion and cognition.
Trained skills	DM, ATT, rumination postponement, activity scheduling later in treatment if necessary	Self-observation by activity protocols, establishing individual goals and values, value-based activity scheduling, interpersonal skill training, problem-solving skill training
Therapeutic strategies	Case Formulation, use of metaphors, socratic dialogue and exercises to explain and train DM and ATT. Cognitive restructuring of metacognitions.	Validation of depressive behavior and thinking, promoting self-observation-techniques (e.g., week schedules) and behavior analysis, acceptance of aversive emotions, promoting opposite action, activation exercises, detailed planning of activities, behavior-oriented skill-training.
Analysis of problem behavior	Use of the case formulation to demonstrate problematic cognitive processes.	Use weekly schedule to link aversive emotions to problematic behavior.
Structure of individual session	ATT at the start of each session and as homework assignment. Focus on dealing with thoughts and other internal events. Usage of metaphors and exercises to illustrate DM as a different way of reacting on thoughts. Reduction of the CAS by teaching skills for dealing with internal events (DM). Activity scheduling in a later state of treatment.	Checking homework assignment and week schedule at start of session. Use of worksheets to work on individual values, interpersonal and problem-solving skills. Focus on behavior change. Session ends with concrete activity scheduling and homework assignment.
Structure of group session	Introduction activity (e.g., DM exercise) and ATT at the beginning of each session. Focus on reduction of CAS and dealing with thoughts and other internal events.	Homework and goal-related opening and closing round. Focus on activity scheduling and activation, including activating exercise and planning weekly activities in each session.

*MCT, Metacognitive Therapy; BA, Behavioral Activation; DM, Detached Mindfulness; ATT, Attention Training Technique; CAS, Cognitive Attentional Syndrome*.

### Assessments

Assessments are scheduled at baseline, pre-treatment, mid-treatment (3 months after treatment start) and treatment completion (6 months after start). Follow-up assessments will be conducted at 12, 18, and 30 months after treatment start. Assessments include interviews (conducted by blind and independent research assistants and clinicians trained in the interviews) and self-report measures (administered by a computer). Assessment time points are summarized in Table 2.

**Table 2 T2:** Interviews and questionnaires used at each assessment.

	**Baseline**	**Pre-treatment**	**Mid-treatment**	**Post-treatment**	**Follow-up assessments**		
			**3 months**	**6 months**	**12 months**	**18 months**	**30 months**
HRSD	•	•	•	•	•	•	•
QIDS-C16	•	•	•	•	•	•	•
SKID-I	•				•	•	•
SKID-II	•				•	•	•
Structured assessment depression	•			•	•	•	•
WHODAS 2.0	•		•	•	•	•	•
Demographic questionnaire	•			•	•	•	•
Medication questionnaire	•		•	•	•	•	•
CTQ	•					
PHQ-9	•		•	•	•	•	•
BSI	•		•	•	•	•	•
SF-12	•		•	•	•	•	•
MDD-S	•		•	•	•	•	•
MCQ-30	•		•	•	•	•	•
RSQ-D	•		•	•	•	•	•
BADS	•		•	•	•	•	•
DERS	•		•	•	•	•	•
CDQ			•	•		

*HRSD, Hamilton Rating Scale for Depression; SCID I, Structured Clinical Interview for DSM-IV Axis-I Disorders; SCID-II, Structured Clinical Interview for DSM-IV Axis-II Disorders; CTQ, Childhood Trauma Questionnaire; QIDS-C16, Quick Inventory of Depressive Symptomatology; Clinician Rating; PHQ, Patient Health Questionnaire; WHODAS 2.0, World Health Organization Disability Assessment Schedule 2.0; BSI, Brief Symptom Inventory; SF-12, Short Form-12 Health Survey; MDD-S, Major Depressive Disorder Scale; MCQ-30, Metacognitions Questionnaire; RSQ-D, Response Style Questionnaire; BADS, Behavioral Activation of Depression Scale; DERS, Difficulties in Emotion Regulation Scale; CDQ, Care Dependency Questionnaire*.

### Outcome measures

#### Primary outcome measure

*Primary outcome measure* is depressive severity assessed by the 24-item version of the Hamilton Rating Scale for Depression (HRSD-24) (47), a semi-structured interview measuring severity of all symptom domains of depression described by the DSM-IV over the last 7 days. The HRSD has shown good psychometric qualities (47, 53). A cutoff of 16 points has been defined as indicating the presence of a moderate depressive episode and a total score of ≥16 points will be handled as inclusion criterion in this study (54). Remission of depression is defined as an HRSD score of ≤ 8, response as a reduction of 50% in the baseline total score of the HRSD (46, 55) and a score of 15 or less, but of more than 8.

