### Statistical analyses

Hypothesis will be tested by performing analyis on the whole database including all randomized patients (intention-to-treat analysis). Multiple imputation procedure will be used to replace missing data. We will use linear mixed models (LMM) as they have the advantage of using all available data of each subject. LMM analyses also offer the opportunity to choose an appropriate covariance structure reflecting the potential dependence due to repeated measurements (77). Adjustment for baseline measure will be chosen as this increases statistical power and accounts for regression to the mean (78). All continuous outcomes will be analysed as change from baseline with a random intercept for the participant, time as within-groups factor, study group as well as gender as fixed effect and adjustment for baseline measure. The study hypothesis will be tested on the main effect for group. The estimation of effect size will be based on the imputated dataset and Cohen's d will be calculated for continuous data and numbers needed to treat (NNT) for binary data. The appropriate forms of mixed regression will be chosen for categorical outcome variables, counts and in case of non-normal residuals (poisson, gamma, negative binominal, etc.). To identify predictors or moderators related to treatment outcome, mixed regression methods will be used.

Negative effects will be identified by analyzing and reporting the amount of participants that experienced a clinical significant deterioration [according to Jacobson and Truax (79)].For the time to event analysis, onset of remission will be used as the dependent variable and group assignment as the independent variable. Here, remission will be defined as a score of < 6 on the weekly QIDS-SR16 rating. Patients who do not achieve remission within the 6 months of treatment or dropped out will be censored. No missing data will be substituted for this analysis. The *Kaplan-Meier method* will be used to estimate time to remission (in weeks) and remission rates. The main hypothesis will be tested by comparing the estimated remission rates in both groups using the log-rank test. *Cox proportional hazards regression* will be used to calculate the hazard ratios, to evaluate the influence of covariates for the adjusted analyses and to perform the subgroup analyses.

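### The HRSD response category leaves out remitted patients, so a response rate or NNT computed on it alone can understate, hide or reverse a real treatment difference

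*Protocol article*

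**What the plan says.** All references are to the protocol article.

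- **Primary outcome measure**, remission: "Remission of depression is defined as an HRSD score of ≤ 8".
- **Primary outcome measure**, response: a 50% reduction in the baseline HRSD total "and a score of 15 or less, but of more than 8". The two categories share a boundary and do not overlap.
- **Eligibility criteria**: patients must "have a depression severity score of 16 or higher" on the 24-item HRSD. Primary outcome measure repeats this: "a total score of ≥16 points will be handled as inclusion criterion in this study".
- **Statistical analyses**: effect sizes are Cohen's d for continuous outcomes and "numbers needed to treat (NNT) for binary data". No binary variable is named there. Mixed regression of a suitable form is planned for categorical outcomes.
- **Sample size**: the outcome for the main hypothesis "is the severity of depressive symptoms at post-treatment, assessed by the Hamilton Rating Scale for Depression". It is continuous and does not use the response definition.

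**The concern.** Response is normally read as a floor of improvement: a patient who does better stays a responder. Here the category also has a lower score limit, so a patient moving from 9 to 8 leaves it by improving. A more effective treatment brings patients into the category from above and moves others out of it into remission. The net change can be small or negative even when the treatment is clearly better.

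If the response rate is compared between MCT and BA on its own, or turned into an NNT, readers could see no difference or the wrong direction. The Discussion expects the trial to feed later meta-analytic comparisons. A response rate that excludes remitters could there be pooled with rates that include them.

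**Working it through.** **1. The plan's own figure.** For two-sided 5%, 80% power, d = 0.5 and 1:1 allocation, the normal approximation gives n = 2 × (1.960 + 0.842)² / 0.5² = 62.8, so 63 per arm. The t-test calculation gives 63.8, so 64 per arm, with power 80.1%. The stated 64 per arm (128 in total) is reproduced. It does not depend on the response definition.

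**2. Which scores qualify (no distributional assumption).** Take the baseline score b as the score meeting the entry criterion, and read the reduction as at least 50%. A later score s is a response if s ≤ b/2 and 9 ≤ s ≤ 15. The number of qualifying integer scores is max(0, min(15, ⌊b/2⌋) − 8).

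| Baseline | Qualifying scores | Count |
|---|---|---|
| 16, 17 | none | 0 |
| 18, 19 | 9 | 1 |
| 24, 25 | 9–12 | 4 |
| 30 or more | 9–15 | 7 |

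For remission, s ≤ 8 and b ≥ 16 give s/b ≤ 8/16 = 0.5. Every remitter thus meets the 50% criterion and is excluded only by the lower limit.

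**3. Effect on a group comparison.** The article gives no HRSD means, SDs, correlations or expected rates, so these are assumptions: baseline mean 24 (SD 5) or 28 (SD 6), restricted to 16 or more; post-treatment SD 7 or 9; baseline–post correlation 0.3 or 0.5; worse-arm post mean 10, 12, 14, 16 or 18; better arm lower by d = 0.5 (3.5 or 4.5 points). That makes 2 × 2 × 2 × 5 = 40 scenarios, each simulated with 500,000 patients per arm and rounded scores. Three of them (worse vs better arm):

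| Scenario | Remission | Response as written | Response with remitters (score 15 or less kept) |
|---|---|---|---|
| A: baseline 28, SD 7, r 0.3, post 10 vs 6.5 | 41.0% vs 60.9% | 29.4% vs 24.5% (−4.9 points, NNT about −20) | 70.4% vs 85.4% (NNT 6.7) |
| B: baseline 24, SD 9, r 0.3, post 12 vs 7.5 | 33.6% vs 53.4% | 16.9% vs 17.1% (NNT about 560) | 50.5% vs 70.5% (NNT 5.0) |
| C: baseline 28, SD 7, r 0.5, post 18 vs 14.5 | 8.1% vs 18.9% | 16.0% vs 25.5% (NNT about 10) | 24.1% vs 44.4% (NNT 4.9) |

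The mechanism is an identity: difference in response as written = difference with remitters − difference in remission.

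- A: 15.0 − 19.9 = −4.9 points
- B: 20.0 − 19.8 = +0.2 points
- C: 20.3 − 10.8 = +9.5 points

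**4. Across all 40 scenarios.** As written, the difference runs from +9.5 to −4.9 points. It is negative in all 8 scenarios with worse-arm post mean 10 (remission about 40 to 43%). It lies between +2.0 and −1.0 points in the 8 with mean 12 (remission about 29 to 34%), and is positive in the other 24. With remitters counted, the better arm leads in all 40 by 15 to 22 points (NNT about 4.5 to 6.7). The NNT for remission is 5.0 to 9.6.

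**5. A separate parameter set.** With baseline mean 25 (SD 6, truncated at 16), post SD 8, correlation 0.4 and post means 12 vs 8 (d = 4/8 = 0.5), response as written is 21.2% vs 21.8% (NNT about 170). Adding remission gives 31.1 + 21.2 = 52.3% vs 50.7 + 21.8 = 72.5%, a difference of 20.2 points and an NNT of about 5.

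**The case against.** The strongest reply is that no planned analysis is tied to this definition. The confirmatory outcome is continuous HRSD-24 severity in a linear mixed model. The secondary outcomes listed in the Introduction do not include HRSD response. The one remission analysis spelled out, time to remission, uses the weekly QIDS-SR16. The NNT sentence names no binary variable, and which endpoints are tabulated is commonly left to a fuller document. All of this stands, and it limits the severity.

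A second reply is that the abutting limits read naturally as a three-way classification: remission, response short of remission, neither. Nothing in the article calls remitters non-responders, and adding the first two levels gives the usual cumulative rate. That reading is coherent. But the article does not state it, labels the middle level simply as response, and does not say that remitters are added back before a rate or NNT is formed.

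A third reply is that reversal depends on assumed remission levels. This also stands: when few remit (scenario C) the direction is right, though diluted. The Introduction does report that only about half of patients treated with CBT remit, which makes the affected range plausible; it does not say that this refers to an HRSD score of 8 or less. Nor would the reversal look striking in a single trial. In scenario A the standard error at 64 per arm is √[(0.294 × 0.706 + 0.245 × 0.755)/64] ≈ 7.8 points against an expected −4.9. The practical loss is that an expected 15-point advantage disappears from the response rate.

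A reader might go further and infer that the planned NNT is meaningless, or that the main result is compromised. The documents support neither. A remission NNT is well defined and unaffected, and the primary test and sample size never use the response category.

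**Conclusion.** The point holds as a minor-to-moderate issue for secondary outcomes. That the category excludes every remitter, cannot be reached from a baseline of 16 or 17, and can be left by improving follows from the article's own thresholds without further assumptions, apart from taking the entry score as baseline and the reduction as at least 50%.

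The size of the distortion is conditional. It rests on assumed HRSD distributions, a true d = 0.5, and response being compared or converted to an NNT by itself, which the article neither states nor rules out. Under those conditions the contrast is diluted when few patients remit, and near zero or wrong-signed when worse-arm remission is about 30 to 40% or more.

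**What to change.** Add one sentence to Primary outcome measure or Statistical analyses, choosing one of two forms:

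1. Any HRSD response rate, response comparison or response NNT counts remitters as responders: at least 50% reduction from baseline and a score of 15 or less, including scores of 8 or less. Remission is reported separately. This keeps the article's upper limit of 15, which sits just below the entry threshold of 16.
2. Rename the present category 'response without remission' and analyse remission, response without remission and non-response as one ordered outcome.

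Under either form, name the binary outcomes for which an NNT will be given. No new data, visits or patients are needed. The choice should be recorded before outcomes are compared by arm, because choosing later between the literal and the cumulative rate could change the reported direction of effect.
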